## Abstract

**Background:**

Pregnancy leads to several skin changes, but evidence about structural and functional skin changes is scarce. Findings on skin structure and function in children in their first year reveal rapid skin maturation, but evidence indicates that in particular, water holding and transport mechanisms are different from adults. Important questions include whether maternal cutaneous properties predict infant skin condition, and if so, how. This is especially relevant for the skin's microbiome because it closely interacts with the host and is assumed to play a role in many skin diseases. Therefore, the study objective is to explore characteristics of skin and hair of pregnant women and their newborns during pregnancy and in the first six months after delivery and their associations.

**Methods:**

The study has an observational longitudinal design. We are recruiting pregnant females between 18 and 45 years using advertisement campaigns in waiting areas of gynecologists and hospital's outpatient services. A final sample size of *n* = 100 women is the target. We perform noninvasive, standardized skin, hair, and skin microbiome measurements. We establish the baseline visit during pregnancy until at the latest four weeks before delivery. We schedule follow-up visits four weeks and six months after birth for mothers and their newborns. We will calculate descriptive statistical methods using frequencies and associations over time depending on scale levels of the measurements. *Discussion*. The majority of previous studies that have investigated infants' skin microbiome and its associations used cross-sectional designs and focused on selected characteristics in small samples. In our longitudinal study, we will characterize a broad range of individual and environmental characteristics of mothers and their newborns to evaluate interrelationships with skin parameters and their changes over time. Considering the combination of these multiple variables and levels will allow for a deeper understanding of the complex interrelationship of the newborn's skin maturation. This trial is registered with ClinicalTrials.gov (Identifier: NCT04759924).

## 1. Background

The skin is widely considered the largest organ of the human body, and it fulfills a variety of essential functions. One of the most important functions is protection. However, there are certain periods in life when skin health is challenged [1]. Two of these periods are during pregnancy for women and during the first few months after birth for both mothers and their newborns. It is well known that pregnant women may undergo a wide range of skin and hair changes such as pigmentary, vascular, hair growth, nail, and connective tissue alterations [2–6]. These effects are also assumed to continue after childbirth [7]. The scalp hair is particularly affected: hormonal changes during pregnancy lead to a high anagen rate of nearly 90% of all hair follicles during the second and third quarters of pregnancy [8]. However, some women experience postpartum diffuse hair loss, which is enhanced in women already having hair loss problems prior to pregnancy. This hair growth disorder is known as telogen effluvium, lasting between six weeks and up to six months after delivery [9]. But why there are significant individual differences in postnatal hair loss remains unclear. So detailed evidence about the structure and function of skin and hair changes during and after pregnancy is largely lacking.

In contrast, evidence about skin function and skin structure in newborns and infants is more common. Immediately after birth, the rapid skin barrier maturation is well studied [10], but evidence indicates that in particular, the water holding and transport mechanisms are very different to adults in the first year of life [11]. Transepidermal water loss (TEWL) measurements indicate that after the first month after birth, TEWL seems to become similar to the adult skin [10, 12, 13]. Until one year of age, TEWL increases [10, 14, 15], and pH values of the skin surface decline from immediately after birth to several months later, indicating skin barrier maturation [10, 15, 16].

In recent years, there has been an increasing interest in associations of the skin microbiome and skin health [17]. The above-described physiological changes of the skin from birth during the first year of life may also interact with the skin microbiome [18]. Oranges et al. conclude that the skin microbiome of newborns resembles the microbiome of moist skin sites in adults [13]. Other study results indicate associations between the richness and diversity of the microbiome, the skin, and environmental properties [18–21]. This signifies complex interrelationships between physiological development, microbial colonization and growth, and external influences.

Until now, few studies have explored possible associations of skin function and microbiome between mothers and newborns. Dominguez-Bello et al. showed that the method of delivery (vaginal or via C-section) is linked to the diversity of the cutaneous bacterial colonization [19]. Additionally, results of 50 mother-child pairs indicate similarities of the children's bacterial genera to those of their own mothers [22]. Other study results suggest associations between environmental conditions, age, and the skin microbiome [23, 24].

However, most study results are based on cross-sectional study designs, ignoring changes over time. Because of the multiple interactions between skin structure, function, and microbiome, it is necessary to consider and measure all aspects over time.

## 2. Methods/Design

### 2.1. Aim

The aim is to measure skin and hair characteristics of mothers and newborns over time and determine demographic, environmental, and health characteristics associated with skin microbiome development.

Therefore, we will answer the following research questions:Are there associations between health, skin, and hair characteristics of mothers and newborns?How does the skin microbiome change during pregnancy and after birth?Do maternal health and skin characteristics predict the skin characteristics of newborns and infants?

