### 2.3. Setting

We invite women after the first pregnancy trimester from the federal state of Berlin (Germany) during their visits to gynecologists and/or midwives. We conduct inclusion and all study visits and measurement procedures at the Clinical Research Center for Hair and Skin Science at the Department of Dermatology at the Charité–Universitätsmedizin Berlin (Germany). If they meet the eligibility criteria, women are included in the study. Upon inclusion in the study after the baseline visit, we follow up with the women and their newborns four weeks after delivery and again six months after delivery.

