### 2.7. Bias

#### 2.7.1. Information Bias

During the study period, the risk of losing participants is addressed with proper information and close support in the beginning and throughout the study. An expense allowance is provided. If a woman is included during the early phase of pregnancy, a phone call is scheduled three months after inclusion or at the latest one week before the due date. This phone call allows us to check the current situation, as well as to check the date for the second visit (t1). Similar to this procedure, the women are called one week before the scheduled third visit (t2). If the women are not reachable, phone calls are repeated twice, and in addition, emails are sent and repeated twice. If there is no response, a letter by registered post is sent. If there is no response after all contact attempts, the woman is then excluded from the study.

In order to estimate the outcomes accurately, all investigations are following internal standardized operating or technical procedures, with staff exclusively allocated to the study performing them.

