### 2.9. Statistical Methods

We will describe the demographic characteristics of the subjects, using absolute and relative frequencies, means, and standard deviations (SD). Metric outcomes will be described using means, SD, medians, and interquartile ranges (IQR) per group and time point. Ordinally, scaled outcomes will be described using medians and IQR per group and time point. Associations of skin parameters between mothers and their newborns/infants will be described using correlation coefficients (Kendall's Tau). Linear mixed models (metric analysis), as well as nonparametric rank-based methods for longitudinal data (ordinal data or skewed endpoints), will be used to assess differences between groups over time (and possible interactions). Furthermore, the Munzel test r (nonparametric) or paired *t* tests (metric observations) will be used to compare paired data. Confidence intervals (95%) will be computed for the effects of interest. Due to the explanatory character of the study, all statistical analyses are exploratory, and thus, all *P*-values and confidence intervals are considered descriptive. If missing values occur, we discuss them on an individual level and use all available cases in the analysis. All statistical methods will be performed using validated software.

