## 3. Discussion

Most of the previous studies investigating the infant's skin microbiome and its associations were conducted using cross-sectional designs and focused on selected characteristics in small samples. In our longitudinal study, we are characterizing a broad range of individual and environmental characteristics of mothers and their newborns to evaluate interrelationships with skin parameters and their changes over the period of at least eight months. Because it is well known that cutaneous changes occur rapidly during and after pregnancy and after birth, the chosen times for measurements are likely to capture these changes. Connecting demographic, environmental characteristics, as well as biophysical skin parameters and the skin microbiome has never been done in this setting to date. Considering these multiple variables and levels together will allow for a deeper understanding of the complex interrelationship of the newborn's skin maturation and allow generating hypotheses to be tested in larger confirmatory studies. By analyzing factors influencing the cutaneous microbiome of the newborns, the results can support recommendations for environmental or individual living conditions and may help predict cutaneous risk in newborns and infants based on their mothers.

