## Figures and Tables

**Table 1 tab1:** Timeline for women and newborns.

	Inclusion baseline visit during pregnancy (16^th^–36^th^ week) t0	Delivery + 4 weeks t1	Delivery + 6 months (end of the study) t2

Informed consent	*x*	*x* newborn	
Inclusion/exclusion criteria	*x*	*x* newborn	
Medical examination	*x*	*x* ^1^	*x* ^1^
Dermatological examination	*x*	*x* ^1^	*x* ^1^
Skin measurements	*x*	*x* ^1^	*x* ^1^
Skin microbiome	*x*	*x* ^1^	*x* ^1^
Hair metrix analysis	*x*	*x* ^1^	*x* ^1^

*x*
^1^ = visit for mother and baby.

**Table 2 tab2:** Variables.

Variables	Statistics/level of scales	Possible range of measurements	Time of measurement Women	Time of measurement Newborn/infant	Source of information
Age	Metric variable	In years, women In days/months, newborn/infant 18–45 years, women 0–28 d, newborn 1–6 months, infant	Baseline, t0	Delivery + 28 d, t1 Delivery + 6 months, t2	ID card, woman “U-heft,” newborn/infant U3: 4^th^–5^th^ week U5: 6^th^–7^th^ month
Weight	Metric variable	In kg, woman In kg, newborn/infant	Baseline, t0 Delivery + 28 d, t1 Delivery + 6 months, t2	Delivery + 28 d, t1 Delivery + 6 months, t2	Measurement “U-heft,” newborn/infant U3: 4^th^–5^th^ week U5: 6^th^–7^th^ month
Height	Metric variable	In cm, woman In cm, newborn/infant	Baseline, t0	Delivery + 28 d, t1 Delivery + 6 months, t2	Self-reporting, woman “U-heft,” newborn/infant U3: 4^th^–5^th^week U5: 6^th^–7^th^month
Sex	Nominal variable	Female Male		Delivery + 28 d, t1	“U-heft,” newborn/infant
					U1 delivery
Habitation	Nominal variable	Urban Rural	Baseline, t0 Delivery + 28 d, t1 Delivery + 6 months, t2	Delivery + 28 d, t1 Delivery + 6 months, t2	Self-reporting, woman
Newborn/infant's environment	Nominal variable	Apartment House		Delivery + 28 d, t1 Delivery + 6 months, t2	Self-reporting, woman
Course of delivery	Nominal variable	Vaginal birth Caesarean	Delivery + 28 d, t1		“U-heft,” newborn/infant U1 delivery
Vaginal seeding	Nominal variable	Yes No		Delivery + 28 d, t1	Self-reporting, woman
Newborn/infant nutrition	Nominal variable	Breastfeeding Cow-milk-based infant formula (including hypoallergenic (HA) based formula) feeding or combination		Delivery + 28 d, t1 Delivery + 6 months, t2	Self-reporting, woman
Period of newborn/infant nutrition (supplementary feeding)	Metric variable	From week *x* to week x		Delivery + 28 d, t1 Delivery + 6 months, t2	Self-reporting, woman
Gestational age at birth	Metric variable	In weeks		Delivery + 28 d, t1	“U-heft,” newborn/infant U1 delivery

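### Research question 2 asks about microbiome change during pregnancy, but each woman is measured once in pregnancy, and the stated eight-month minimum span is not guaranteed by the schedule

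*Protocol article*

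**What the plan says.** Section 2.1 lists as its second research question "How does the skin microbiome change during pregnancy and after birth".

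Table 1 has one column before delivery, headed "Inclusion baseline visit during pregnancy (16^th^–36^th^ week) t0". The abstract sets the latest timing of that visit: "We establish the baseline visit during pregnancy until at the latest four weeks before delivery". The other two visits come after birth; Section 2.3 says "we follow up with the women and their newborns four weeks after delivery and again six months after delivery". Table 2 lists the maternal microbiome at these same three points. The only contact described between t0 and t1 is in Section 2.7.1, for women who enter early: "a phone call is scheduled three months after inclusion or at the latest one week before the due date". That call checks the situation and the next appointment, and no swab is taken.

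On analysis, Section 2.9 says "Metric outcomes will be described using means, SD, medians, and interquartile ranges (IQR) per group and time point". Linear mixed models and rank-based longitudinal methods "will be used to assess differences between groups over time (and possible interactions" are also named there, without stating how time is coded or which covariates enter. Table 2 records gestational age at birth but does not list gestational week at t0.

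The Discussion describes skin parameters and "their changes over the period of at least eight months".

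**The concern.** To see change during pregnancy within a woman, at least two pregnancy measurements are needed. With one per woman, any trend across pregnancy is a comparison of different women seen at different weeks. The Background faults earlier work for exactly this kind of cross-sectional evidence. The Discussion adds that skin changes are rapid in this period and that the chosen visits should catch them. If change is rapid, one visit in a 20-week window cannot do so.

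The same window affects the question that the design can answer. A t0 value from week 16 and one from week 36 count as the same time point in the descriptive summaries, so the average difference between t0 and t1 depends partly on when women happened to enrol. A report that follows the article could present that difference as change during pregnancy, which the data would not support.

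Finally, the minimum span in the Discussion can be checked against the visit schedule, and it does not follow from it.

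**Working it through.** **Inputs.** From the article: t0 in weeks 16 to 36 (Table 1) and no later than four weeks before delivery (abstract); t1 at delivery plus 4 weeks; t2 at delivery plus 6 months. Assumed: delivery at week 40 as the reference case, since the article gives no delivery week; 4.348 weeks per month, so 6 months = 26.1 weeks.

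**1. Pregnancy measurements per woman.** Counted from Tables 1 and 2: one. Within-woman change in pregnancy has no second value to be computed from.

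**2. Interval from t0 to t1** = (delivery week − week at t0) + 4.
- t0 at week 36: (40 − 36) + 4 = 8 weeks.
- t0 at week 16: (40 − 16) + 4 = 28 weeks.

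**3. The stated minimum of eight months.** Span from t0 to t2 in months = (delivery week − week at t0)/4.348 + 6.

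| Week at t0 (delivery at week 40) | Span, months |
|---|---|
| 16 | 24/4.348 + 6 = 11.5 |
| 30 | 10/4.348 + 6 = 8.3 |
| 32 | 8/4.348 + 6 = 7.8 |
| 36 | 4/4.348 + 6 = 6.9 |

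The stated minimum is not reproduced. The last row needs no assumption about delivery week, because a t0 visit four weeks before delivery gives 6.9 months whenever birth occurs (7.0 if a month is counted as four weeks). Eight months requires t0 at least 2 × 4.348 = 8.7 weeks before delivery, which is week 31.3 for a week-40 birth.

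Share of women below eight months, if entry were uniform over weeks 16 to 36 (assumption):
- Delivery at week 40: (36 − 31.3)/20 = about 24%.
- Delivery at week 42: (36 − 33.3)/20 = about 14%.
- Delivery at week 37, with t0 capped at week 33 by the four-week limit: (33 − 28.3)/(33 − 16) = about 28%.

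Infants are observed from 4 weeks to 6 months: 6 − 4/4.348 = about 5.1 months.

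**4. Effect of pooling t0.** For uniform entry, the variance of week at t0 is 20²/12 = 33.3 (SD 5.8 weeks). If an outcome shifts linearly by c SD over the window, ignoring week adds (c/20)² × 33.3 to a within-week variance of 1:
- c = 0.5: 0.021, about 2%.
- c = 1: 0.083, about 8%.
- c = 1.5: 0.188, about 19%.

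**5. What a between-woman trend could deliver.** Under the same uniform entry, the 95% half-width of the estimated 20-week difference is 1.96 × 20/(5.77 × √n) residual SDs: 0.68 for n = 100 and 0.55 for n = 150. This is estimable but imprecise, and it remains cross-sectional.

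**The case against.** The strongest reply is that the second research question has an ordinary reading that the design serves. The abstract and Section 2.2 describe a cohort followed through pregnancy and the period after it, so the question can mean change from pregnancy to after birth. That reading is answerable with t0, t1 and t2. It reduces the defect to wording, but the literal text promises more, and no later analysis plan can supply a missing visit.

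A reader might infer that the mixed models treat time as three categories. The article does not say so. Section 2.9 fixes handling by time point only for the descriptive summaries, and time coding and covariates may be settled in the full protocol, which is not shown. The absence of a gestational-week term from the article is therefore not an error in itself.

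A reader might also infer that gestational week at t0 confounds any prediction of infant outcomes from maternal t0 values. That would require week of recruitment to be related to infant skin at t1 or t2, and the article gives no such link. Without one, the spread of weeks adds noise to the maternal predictor.

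Lastly, it is fair that the eight-month remark sits in the Discussion and feeds no analysis, and that most women would reach eight months under uniform entry. Nor should the shortfall be pushed lower by pairing a week-36 visit with a week-37 birth (6.2 months), because that visit would breach the four-week limit in the abstract.

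**Conclusion.** The point holds in limited form. Within-woman microbiome change during pregnancy is not observed; change from pregnancy to after birth is. This follows from the visit schedule alone. The minimum span is misstated: the schedule allows about 6.9 months, and at a week-40 delivery women with t0 after about week 31 fall short. It would be wrong to say that eight months is never reached.

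Pooling weeks 16 to 36 adds heterogeneity to the t0 contrast and to t0 values used as predictors. The size is modest and rests on the assumed linear shift and uniform entry. Confounding is not shown.

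Severity is minor to moderate. Section 2.9 treats all P-values and intervals as descriptive, Section 2.8 makes no formal sample size calculation, and the remedy needs no new visit. What matters is that the conclusions claimed match what was measured.

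**What to change.** 1. Reword the second research question to change from pregnancy (weeks 16 to 36) to after birth. State that any trend by gestational week within pregnancy is a between-woman, cross-sectional estimate.
2. Derive gestational week at t0 as gestational age at birth minus the weeks from the t0 visit to the birth. Include it, or time relative to delivery, in the longitudinal models and in models that use t0 values as predictors. Gestational age at birth is already in Table 2; visit and birth dates should be on file. For women lost before t1, keep the week established at inclusion, which is needed anyway to check the t0 window.
3. In the Discussion, restate the span as about 7 to 11.5 months for mothers (week-40 delivery) and about 5 months for infants.

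The cost is two text edits, one derived variable and one model term. The claims become slightly narrower.

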### 2.2. Study Design

We perform a longitudinal, descriptive cohort study including females during pregnancy and puerperium, and their newborns until six months of age shown in Table 1.

### 2.3. Setting

We invite women after the first pregnancy trimester from the federal state of Berlin (Germany) during their visits to gynecologists and/or midwives. We conduct inclusion and all study visits and measurement procedures at the Clinical Research Center for Hair and Skin Science at the Department of Dermatology at the Charité–Universitätsmedizin Berlin (Germany). If they meet the eligibility criteria, women are included in the study. Upon inclusion in the study after the baseline visit, we follow up with the women and their newborns four weeks after delivery and again six months after delivery.

### 2.4. Participants

Participants are pregnant females between 18 and 45 years old and residing in Berlin (Germany). Prerequisites for study inclusion are individual written informed consent, clinically healthy skin and hair appearance, as well as being free of any dermatological condition. Skin afflictions, which may interfere with the study assessments, especially atopic dermatitis, scars, or other lesions at the investigational site result in exclusion. Women must be of general good and stable health as confirmed by medical history and by a physical examination. They must accept to abstain from sunbathing and solariums and to agree to stay consistent in using their individual skin cleaning and caring routines during the study.

Women are excluded due to regular smoking, regular alcohol intake, or criteria related to diseases such as any dermatological condition or skin affliction, which may interfere with the study assessments. These could be any inflammatory dermatosis (psoriasis, atopic dermatitis, or other lesions at the investigational sites) or clinically significant, possibly unstable medical conditions due to pregnancy such as gestosis, eclampsia, or thrombosis. Criteria related to treatments and products such as current topical or systemic treatment possibly affecting the skin (diuretics, cholesterol-lowering drugs, and hormones) during the past four weeks are further exclusion criteria. Additionally, therapeutic ultraviolet radiation or increased ultraviolet exposure within six weeks before inclusion leads to exclusion. For safety, other medical reasons, and any individual reasons, study participation can be stopped.

### 2.5. Variables

Due to the descriptive and exploratory nature of this study, we assess a broad range of characteristics and variables. Skin structure is measured by means of skin surface topography, epidermal thickness, skin stiffness, and skin elasticity. Skin function is measured by means of stratum corneum hydration (SCH), TEWL, and skin surface pH, which are established parameters to characterize the skin barrier function. Skin microbiome is defined as bacterial diversity, and in this study, the relative abundance of phylotypes, (operational taxonomic units, OTUs) will be measured. Hair growth is measured on the central and occipital scalp by means of hair density and hair widths. The definitions of the variables are shown in Table 2 and further explained in the following paragraph.

